## 5. ANALYSIS POPULATIONS

Analysis sets for the pooled and interim analyses are defined in [Table 3](#). The groups/participants meeting any of the conditions below will be excluded from all analysis sets (unless otherwise indicated) regardless if they meet the definition in [Table 3](#).

- Groups without randomization (eg, group 3 of COV001, group 11 of COV002);
- Participants previously vaccinated with a ChAdOx1 vectored vaccine (eg, group 11 of COV002);
- Participants with HIV diagnosed at study start (group 3 of COV005 and group 12 of COV002).
- Children (< 18 years old)

Furthermore, only groups evaluated for efficacy in COV002 (ie, groups 4, 6, 9,10) will be considered in populations for efficacy analysis.

The corresponding control group for group 2d in COV001 is group 2e.

All analyses will be performed by actual treatment received. For primary endpoint, a sensitivity analysis by randomized treatment assignment will be performed.

Table 3 Populations for Analysis

| Population                    | Description                                                                                                                                                                                                                                                                                                                                                                                                                                                                                                                                                                                            |
|-------------------------------|--------------------------------------------------------------------------------------------------------------------------------------------------------------------------------------------------------------------------------------------------------------------------------------------------------------------------------------------------------------------------------------------------------------------------------------------------------------------------------------------------------------------------------------------------------------------------------------------------------|

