## 10.2 Clinical Laboratory Results

Clinical laboratory results on scheduled visits for COV001, COV002 and COV005 (group 1 and 3 only) will be pooled to examine the most extreme value encoded in the 30 days post dose 1 and 30 days post dose 2 by treatment group and severity grade. The strategy for severity grading across different studies is provided in [Appendix C](#).

The clinical laboratory tests include:

- Haematology; Full Blood Count
- Biochemistry; Sodium, Potassium, Urea, Creatinine, Albumin, Liver Function Tests (ALT, ALP, Bilirubin)

A listing for clinical laboratory results and a listing for laboratory results with toxicity grading scale  $\geq 3$  will be provided at the primary analysis.

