## **Appendix C Pooling and Severity Grading of Laboratory Assessed on Scheduled Visits**

In Studies COV001, COV002, and COV005, the severity of laboratory toxicity from scheduled assessments will be assessed on scales of Grades 1-4. In Studies COV001 and COV002, these laboratory abnormalities will be assessed according to grading scales that have been adapted from the US FDA Toxicity Grading Scale for Healthy and Adolescent Volunteers Enrolled in Preventive Vaccine Clinical Trials ([FDA 2007](#)), using identical grading scales. In Study COV005, laboratory toxicity will be assessed using grading scales adapted from the DAIDS Table for Grading the Severity of Adult and Pediatric Adverse Events, Corrected Version 2.1 ([NIH 2017](#)).

In order to pool laboratory abnormalities from these studies, all pooled data will be uniformly graded using the US FDA grading system as the common grading system. (Note: Study COV003 does not contribute data to this pooling as the study does not have scheduled laboratory assessments.) For the purposes of reporting, values which do not meet at least the criteria of Grade 1 will be reported as normal, to account for results falling between the upper limit of normal for individual laboratories and the lower limit for Grade 1 toxicity. For those variables in which US FDA severity gradings are based upon multiples of the upper limit of the normal reference range (ie, alanine transaminase, alkaline phosphate, and bilirubin), study specific reference ranges will be used.

[Table C1](#) presents the severity gradings that will be used for pooled laboratory abnormalities from Studies COV001, COV002, and COV005. [Table C2](#) presents a comparison of the US FDA severity grade criteria with the 3 studies' individual criteria.

| Table C1 Laboratory Abnormality Severity Grade Criteria to be Used for Pooled COV1, COV002, and COV005 Data |                            |                     |                |                |                |                |                                                                            |
|--------------------------------------------------------------------------------------------------------------------|----------------------------|---------------------|----------------|----------------|----------------|----------------|----------------------------------------------------------------------------|

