| Neutrophils-Decreased                                                                                              | cells × 10  /L | -                   | 1.50-2.00      | 1.00-1.49      | 0.50-0.90      | <0.50          | FDA values. COV001, COV002                                                 |
| Lymphocytes-Decreased                                                                                              | cells × 10  /L | -                   | 0.750-1.000    | 0.500-0.749    | 0.250-0.499    | <0.250         | FDA values. COV001, COV002                                                 |
| Eosinophils-Elevated                                                                                               | cells × 10  /L | -                   | 0.650-1.500    | 1.501-5.000    | >5.000         | -              | FDA values. COV001, COV002                                                 |
| Sodium-Elevated                                                                                                    | mmol/L                     | -                   | 144-145        | 146-147        | 148-150        | >150           | FDA values                                                                 |
| Sodium-Decreased                                                                                                   | mmol/L                     | -                   | 132-134        | 130-131        | 125-129        | >125           | FDA values. COV001, COV002                                                 |
| Potassium-Elevated                                                                                                 | mmol/L                     | -                   | 5.1-5.2        | 5.3-5.4        | 5.5-5.6        | >5.6           | FDA values                                                                 |
| Potassium-Decreased                                                                                                | mmol/L                     | -                   | 3.5-3.6        | 3.3-3.4        | 3.1-3.2        | <3.1           | FDA values.                                                                |

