|                                                                                                                      |                            | Cov005 (DAIDS)  | -                   | N.A.           | N.A.           | N.A.           | N.A.           |
| White Blood Cells- Decreased                                                                                         | cells × 10  /L | FDA             | -                   | 2.5-3.5        | 1.5-2.49       | 1.0-1.49       | <1.0           |
|                                                                                                                      |                            | COV001 COV002   | 4.0-11              | 2.5-3.5        | 1.5-2.49       | 1.0-1.49       | <1.0           |
|                                                                                                                      |                            | Cov005 (DAIDS)  | -                   | 2.00-2.49      | 1.50-1.99      | 1.00-1.49      | <1.0           |
| Platelets-Decreased                                                                                                  | cells × 10  /L | FDA             | -                   | 125-140        | 100-124        | 25-99          | <25            |
|                                                                                                                      |                            | COV001 COV002   | 150-400             | 125-140        | 100-124        | 25-99          | <25            |
|                                                                                                                      |                            | COV005 (DAIDS)  | -                   | 100-< 125      | 50-<100        | 25-<50         | < 25           |
| Neutrophils-Decreased                                                                                                | cells × 10  /L | FDA             | -                   | 1.5-2.00       | 1.0-1.49       | 0.5- 0.99      | <0.50          |
|                                                                                                                      |                            | COV001 COV002   | 2.0-7.0             | 1.5-1.99       | 1.0-1.49       | 0.5-0.99       | <0.50          |

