|                                                                                                                      |                            | COV001 COV002  | 0.02-0.5     | 0.65-1.5             | 1.51-5.00            | >5.00                | Hypereosinophilic                   |
|                                                                                                                      |                            | COV005         | -            | N.A.                 | N.A.                 | N.A.                 | N.A.                                |
| Sodium-Elevated                                                                                                      | mmol/L                     | FDA            | -            | 144-145              | 146-147              | 148-150              | >150                                |
|                                                                                                                      |                            | COV001 COV002  | 134-145      | 146-147              | 148-149              | 150-155              | >155                                |
|                                                                                                                      |                            | COV005 (DAIDS) | -            | 146 to < 150         | 150 to < 154         | 154 to < 160         | ≥ 160                               |
| Sodium-Decreased                                                                                                     | mmol/L                     | FDA            | -            | 132-134              | 130-131              | 125-129              | <125                                |
|                                                                                                                      |                            | COV001 COV002  | 135-145      | 132-134              | 130-131              | 125-129              | <125                                |
|                                                                                                                      |                            | COV005 (DAIDS) | -            | 130-< 135            | 125-< 130            | 121-< 125            | ≤120                                |

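### Table C1, the operative grading table for pooled laboratory data, contradicts the FDA rows of Table C2 on low sodium, neutrophils and urea, and the place of COV005 group 3 in the pool is unresolved

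*SAP*

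**What the plan says.** SAP Appendix C chooses the US FDA scale as the common grading system. It names Table C1 as the table that grades the pooled data and Table C2 as a comparison of the FDA criteria with each study's own. It also sets a default: "values which do not meet at least the criteria of Grade 1 will be reported as normal". The stated reason is to cover results lying between a laboratory's upper limit of normal and the start of Grade 1.

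For Sodium-Decreased, Grades 1 to 4 in Table C1 read "132-134 | 130-131 | 125-129 | >125 | FDA values. COV001, COV002". The FDA row of Table C2 reads "132-134 | 130-131 | 125-129 | <125". For neutrophils, Table C1 reads "1.50-2.00 | 1.00-1.49 | 0.50-0.90 | <0.50" and the FDA row of Table C2 reads "1.5-2.00 | 1.0-1.49 | 0.5- 0.99 | <0.50".

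On who enters the pool, Section 10.2 says: "Clinical laboratory results on scheduled visits for COV001, COV002 and COV005 (group 1 and 3 only) will be pooled". Section 5 lists, among those removed from every analysis set, "Participants with HIV diagnosed at study start (group 3 of COV005 and group 12 of COV002"), but allows exceptions where the plan indicates one. Section 10 ties the safety summaries to the analysis sets of Table A2.

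Section 10.2 asks for a table of the most extreme value by severity grade within 30 days of each dose. It also asks for two listings at the primary analysis: one of laboratory results, and one limited to Grade 3 or higher.

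**The concern.** A programmer told to use Table C1 will code Table C1. Where it departs from the FDA criteria it claims to reproduce, the severity table and the Grade ≥3 listing inherit the error. The two main errors run in both directions: normal sodium values are promoted to the top grade, while the lowest sodium values and some Grade 3 neutrophil counts lose their grade. The sodium error would probably be noticed, because almost everyone would appear as Grade 4. The neutrophil gap might not be, because the output would still look plausible.

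The question about group 3 is separate. As the text stands, two programmers could build different laboratory pools and each cite a section of the SAP.

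**Working it through.** No power or alpha calculation is involved. The check applies the Table C1 cut-offs as printed, takes the highest grade met, and compares the result with the FDA rows of Table C2.

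| Test | Table C1 | Table C2, FDA row |
|---|---|---|
| Sodium-Decreased, Grade 4 (mmol/L) | >125 | <125 |
| Neutrophils, Grade 3 (×10⁹/L) | 0.50-0.90 | 0.5-0.99 |
| Urea, Grades 1 and 2 (mmol/L) | 8.2-9.4 and 9.5-11.0 | 8.2-9.3 and 9.4-11.0 |

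**Sodium, in steps of 1 mmol/L.** The COV001/COV002 row of Table C2 begins "COV001 COV002 | 135-145 | 132-134", so the normal range is 135-145.
- Normal range: the lowest value, 135, already exceeds 125, so all 11 integer values are Grade 4 under Table C1. Under Table C2 none has a low-sodium grade.
- Grades 1 and 2 and the upper part of Grade 3 (132-134, 130-131, 126-129): all exceed 125, so all also meet Grade 4. Only 125 stays Grade 3 alone.
- Below 125, for example 120: not above 125 and not within 125-134, so no grade under Table C1 and Grade 4 under Table C2.

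Taking the first grade met instead of the highest would restore Grades 1 to 3. It would not change the result for the normal range or for values below 125.

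**Neutrophils, in steps of 0.01.** In Table C1 nothing covers the interval between 0.90 and 1.00. That leaves (0.99 − 0.91)/0.01 + 1 = 9 values without a grade. All nine lie within 0.5-0.99, which is Grade 3 in Table C2. With the Table C2 cut-offs, no value from 0 to 2.00 is ungraded. The gap needs counts reported to two decimals: at one decimal, 0.9 is Grade 3 and 1.0 is Grade 2. Table C1 writes its cut-offs to two decimals; the SAP does not state the precision of the data.

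**Urea.** A value of 9.4 is Grade 1 in Table C1 and Grade 2 in both the FDA and the COV001/COV002 rows of Table C2.

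**Other cells.** These three are the numerical mismatches. Table C1 also omits non-numerical Grade 4 terms that stand in the FDA rows of Table C2: dialysis for urea and creatinine, and the hypereosinophilic entry for eosinophils.

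**The default rule.** The criteria expressed as multiples of the upper limit of normal show why its wording matters. If ratios are not rounded to one decimal, ALT with a limit of 45 U/L falls between Grade 1 (to 2.5 × 45 = 112.5) and Grade 2 (from 2.6 × 45 = 117) at 113-116. Read literally, the rule calls those values normal as well. This gap is in both tables.

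**Pool membership.** Section 10.2 names COV005 group 3. Section 5 identifies that group as the HIV group and excludes it, subject to stated exceptions. The Table A2 sets rest on those exclusions. Section 10.2 neither says that it is making an exception nor mentions COV002 group 12, the other HIV group.

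**The case against.** The sodium cell is plainly a slip of one character. The row is headed as a decrease, Grade 3 is 125-129, the comment column cites FDA values, and Table C2 gives <125 for both the FDA and the COV001/COV002 rows. The intended value is recoverable. That stands, and a reader should not infer that the pooled tables are bound to report nearly everyone as Grade 4. That happens only if Table C1 is coded literally and nobody notices. It does not justify leaving the wrong symbol in the operative table.

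A reader might also infer that the plan deliberately classes neutrophil counts of 0.91-0.99 as normal, or that such counts vanish from the report. The documents do not support either reading. The reason given for the default rule covers only results between the upper limit of normal and Grade 1, so on a purposive reading these counts are ungraded, not normal. They would also still appear in the unfiltered laboratory listing. What remains is that they lose their grade in the severity table and drop out of the Grade ≥3 listing.

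On group 3, it is tempting to call Sections 5 and 10.2 flatly contradictory. Section 5 permits exceptions, and naming the group in Section 10.2 may be one. Alternatively, Section 10.2 may only describe which COV005 groups have scheduled laboratory data, with the Table A2 sets still removing group 3. The SAP does not settle which reading applies. Nor does it say that haematology differs in that group, so no bias from including it can be claimed from this document.

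**Conclusion.** The point holds as an error in the operative grading table. Coded as printed, Table C1 inverts low-sodium grading, leaves neutrophil counts of 0.91-0.99 ungraded, and moves urea 9.4 by one grade. The first two alter the Grade ≥3 listing. The result assumes that Table C1 is followed literally and, for neutrophils, that counts are reported to two decimals. The effect cannot be expressed in participants: the SAP holds no laboratory data and gives no sizes for the COV005 groups. No efficacy analysis depends on it.

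The group 3 question is an ambiguity to be resolved, not a proven wrongful inclusion.

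**What to change.** - **Table C1:** align it with the FDA rows of Table C2: Sodium-Decreased Grade 4 as <125, neutrophil Grade 3 as 0.50-0.99, and a single urea boundary in both tables. State whether the omitted non-numerical Grade 4 terms are left out on purpose.
- **Default rule:** limit reporting as normal to values on the normal side of the Grade 1 limit, and state how values between two printed grades are rounded or assigned.
- **Sections 5, 10 and 10.2:** name the laboratory analysis set. Either remove COV005 group 3 from the pool, or declare the exception and show that group separately. Treat COV002 group 12 in the same way.
- **Table 7:** at the same time, check the diastolic Grade 3 entry of > 1100 mmHg against its source. Next to a Grade 2 of 96-100 it is evidently a misprint, and it is minor.

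These are text edits made before programming and need no new data. If group 3 is removed, the COV005 contribution to the pooled laboratory table becomes smaller.
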